| Study procedures | 
Eligible subjects with ES-SCLC were randomly assigned to 3 treatment groups (intervention arm 1, intervention arm 2, and control arm). The treatment was divided into two stages: the induction stage and the maintenance stage.
 
Stage 1: induction stage (21-day cycle for 4 cycles)
 
The planned dose and scheme will follow the scheme below:
 
Intervention arm 1: 1200 mg intravenous TQB2450 on day 1; 12 mg oral anlotinib once daily on days 1-14; intravenous carboplatin at AUC 5 mg/mL/min on day 1 (the maximum dose was 750 mg); 100 mg/m^2 intravenous etoposide on days 1-3;
 
Intervention arm 2: 0 mg intravenous TQB2450 placebo on day 1; 12 mg oral anlotinib once daily on days 1-14; intravenous carboplatin at AUC 5 mg/mL/min on day 1 (the maximum dose was 750 mg); 100 mg/m^2 intravenous etoposide on days 1-3;
 
Control arm: 0 mg intravenous TQB2450 placebo on day 1; 0 mg oral anlotinib once daily on days 1-14; intravenous carboplatin at AUC 5 mg/mL/min on day 1 (the maximum dose was 750 mg); 100 mg/m^2 intravenous etoposide on days 1-3;
 
Stage 1: maintenance stage (21-day cycle)
                                                                                                                                                                                                                                                                                                                       |

|                         |                                                                                                                                                                                                                                                                                                                                                                                                                                                                                                                                                                                                                                                                                                                                                                                                                                                                                                                                                                                                                                                                                                                                                                                                                                                                                                                                                                                                                                                                                                                                                                                                                                                                                                                                                         |
|-------------------------|---------------------------------------------------------------------------------------------------------------------------------------------------------------------------------------------------------------------------------------------------------------------------------------------------------------------------------------------------------------------------------------------------------------------------------------------------------------------------------------------------------------------------------------------------------------------------------------------------------------------------------------------------------------------------------------------------------------------------------------------------------------------------------------------------------------------------------------------------------------------------------------------------------------------------------------------------------------------------------------------------------------------------------------------------------------------------------------------------------------------------------------------------------------------------------------------------------------------------------------------------------------------------------------------------------------------------------------------------------------------------------------------------------------------------------------------------------------------------------------------------------------------------------------------------------------------------------------------------------------------------------------------------------------------------------------------------------------------------------------------------------|
|                         | 
Participants with maintenance therapy will be administered until loss of clinical benefit, unacceptable toxicity, progressive disease (PD), or unsuitable continued medication as determined by the investigators. During maintenance therapy, patients were allowed to receive prophylactic cranial irradiation (PCI), but not radical thoracic radiotherapy (TR). The maintenance stage will be administered as follows:
 
Intervention arm 1: 1200 mg intravenous TQB2450 on day 1; 12 mg oral anlotinib once daily on days 1-14;
 
Intervention arm 2: 0 mg intravenous TQB2450 placebo on day 1; 12 mg oral anlotinib once daily on days 1-14;
 
Control arm: 0 mg intravenous TQB2450 placebo on day 1; 0 mg oral anlotinib placebo once daily on days 1-14;
 
Dose reduction:
 
Anlotinib: A maximum of two dose reductions of anlotinib (to 10/0 mg, 8/0 mg, and then discontinuation) was allowed according to drug-related AEs and cross-dose adjustment is not permitted. For subjects with a dose reduction to 10/0 or 8/0 mg, if subjects may experience disease progression per the investigators but still benefit from the increased dose after a period of medication, subjects could resume only one reduced dose when the safety profile is stable and cross-dose adjustment is not permitted.
 
TQB2450: No dose reduction will be considered.
 
Efficacy is assessed every 2 cycles. Subjects with disease control and tolerable AEs will continue treatment until loss of clinical benefit, unacceptable toxicity, PD, or unsuitable continued medication as determined by the investigators.
 
No other antitumor therapies will be considered during the study treatment.
 |
| Criteria for evaluation | 
Safety:
 
The AEs will be assessed by the NCI-CTCAE v5.0.
 
Efficacy:
 
Response to treatment will be mainly based on RECIST v1.1, and meanwhile iRECIST for further confirmation of the efficacy. Namely, patients diagnosed with PD according to RECIST v1.1 were further identified by iRECIST to determine whether to take further observation.
                                                                                                                                                                                                                                                                                                                                                                                                                                                                                                                                                                                                                                                                                                                                                                                                                                                                                                                                                                                                                                                                                                                                                                                                                                                                                                                                                                 |
| Safety monitoring       | Hemanalysis, urinalysis and stool analysis, biochemistry, 12-lead electrocardiogram, thyroid function, coagulation function, etc.                                                                                                                                                                                                                                                                                                                                                                                                                                                                                                                                                                                                                                                                                                                                                                                                                                                                                                                                                                                                                                                                                                                                                                                                                                                                                                                                                                                                                                                                                                                                                                                                                       |
| Duration of trial       | Aug 2019-Dec 2022                                                                                                                                                                                                                                                                                                                                                                                                                                                                                                                                                                                                                                                                                                                                                                                                                                                                                                                                                                                                                                                                                                                                                                                                                                                                                                                                                                                                                                                                                                                                                                                                                                                                                                                                       |

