## TABLES

**Table S1. Tumor response as assessed by investigator review using RECIST 1.1.**

|                                 | Benmelstobart+Anlotinib+EC
group (N=246) | Anlotinib+EC
group (N=245) | EC alone group
(N=247) |
|---------------------------------|---------------------------------------------|-------------------------------|---------------------------|
| Objective confirmed response    |                                             |                               |                           |
| No. of patients                 | 188 (76.4)                                  | 187 (76.3)                    | 145 (58.7)                |
| 95% CI                          | 70.6-81.6                                   | 70.5-81.5                     | 52.3-64.9                 |
| P value                  | <0.0001                                     | <0.0001                       | Reference                 |
| Best objective response-no. (%) |                                             |                               |                           |
| CR                              | 1 (0.4)                                     | 1 (0.4)                       | 0                         |
| PR                              | 187 (76.0)                                  | 186 (75.9)                    | 145 (58.7)                |
| SD                              | 32 (13.0)                                   | 36 (14.7)                     | 64 (25.9)                 |
| PD                              | 12 (4.9)                                    | 7 (2.9)                       | 23 (9.3)                  |
| NE*                             | 14 (5.7)                                    | 15 (6.1)                      | 15 (6.1)                  |

Differences in response rate between the treatment groups were assessed with the stratified Cochran-Mantel-Haenszel test. *P* values are two-sided.

\* The best overall response could not be evaluated for patients who had no baseline or no postbaseline tumor assessments, and at least one lesion that could not be evaluated.

No.=number; CI, confidence interval; CR=complete response; PR=partial response; SD=stable disease; PD=progressive disease; NE=Not evaluated; EC=Etoposide/carboplatin.

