**Table S2. Tumor response as assessed by investigator review using iRECIST.**

|                                 | Benmelstobart+Anlotinib+EC
group (N=246) | Anlotinib+EC
group (N=245) | EC alone group
(N=247) |
|---------------------------------|---------------------------------------------|-------------------------------|---------------------------|
| Objective response              |                                             |                               |                           |
| No. of patients                 | 157 (63.8)                                  | 139 (56.7)                    | 112 (45.3)                |
| 95% CI                          | 57.5-69.8                                   | 50.3-63.0                     | 39.0-51.8                 |
| P value                  | <0.0001                                     | 0.0114                        | Reference                 |
| Best objective response-no. (%) |                                             |                               |                           |
| CR/iCR                          | 1 (0.4)                                     | 0                             | 0                         |
| PR/iPR                          | 156 (63.4)                                  | 139 (56.7)                    | 112 (45.3)                |
| SD/iSD                          | 27 (11.0)                                   | 29 (11.8)                     | 54 (21.9)                 |
| PD                              | 5 (2.03)                                    | 3 (1.2)                       | 12 (4.9)                  |
| iUPD                            | 14 (5.7)                                    | 13 (5.3)                      | 8 (3.2)                   |
| iCPD                            | 29 (11.8)                                   | 46 (18.8)                     | 46 (18.6)                 |
| NE*                             | 14 (5.7)                                    | 15 (6.1)                      | 15 (6.1)                  |

Differences in response rate between the treatment groups were assessed with the stratified Cochran-Mantel-Haenszel test. *P* values are two-sided.

\* The best overall response could not be evaluated for patients who had no baseline or no postbaseline tumor assessments, and at least one lesion that could not be evaluated.

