## 5.4 Disease Progression

Since similar drugs of TQB2450 induced pseudo-progression in the clinical administration, the efficacy evaluation will be assessed by RECIST v1.1 and further confirmed by iRECIST criteria. That is, patients identified as having disease progression as per RECIST v1.1 will be confirmed by iRECIST to determine further treatment.

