## 9. Efficacy Evaluation

Since similar drugs of TQB2450 induced pseudo-progression in the clinical administration, the efficacy evaluation will be assessed by RECIST v1.1 and further confirmed by iRECIST criteria. That is, patients identified as having disease progression as per RECIST v1.1 will be confirmed by iRECIST to determine further treatment.

Efficacy will be assessed every 2 cycles from cycle 1 day 1 until the radiologically confirmed disease progression. The frequency of radiographic assessments is independent of dose delays and/or dose interruptions. For subjects who discontinue the study drug for reasons other than disease progression, the tumor assessment will still be conducted every 2 cycles until starting a new antitumor therapy, disease progression, withdrawal of consent, or death, whichever occurs first.

The methods of radiographic assessment (CT or MRI) will be determined by the investigator. However, the assessment methods, machines, and technical parameters should be consistent throughout the study period. Contrast media is required for subjects without contraindications. For subjects who had received a radiographic assessment within 14 days before the first dose using the same procedure in the same center, the radiographic assessment could be used as the baseline data in this trial. The baseline tumor assessment should include enhanced CT or MRI of the chest, abdomen, and pelvis (except for subjects with an allergy to contrast media). During the screening period, a cranial plain scan plus enhanced MRI, and bone scan is required for all subjects. However, for subjects without bone metastases, whether the bone scan is performed will be decided by the investigator according to the symptoms. All suspected lesions will be evaluated by imaging. For subjects with bone metastases, the lesions will be monitored using a bone scan. If there is no exacerbation of clinical symptoms in these subjects, re-examination is not required at each visit for tumor assessment; otherwise, a timely re-examination is necessary. An unplanned tumor evaluation should be performed for subjects with suspected disease progression before the next planned evaluation. The radiographic assessment will only be conducted for lesions, but suspected lesions will also be evaluated by imaging.

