### (3) Type I error control for interim efficacy analysis based on OS

One interim analysis for OS is planned for this trial after 70% of the planned OS events (348 cases). If expected efficacy is observed, early declaration of the trial due to efficacy would be considered. The interim analysis will be conducted by iDMC.

Type I error will be controlled by the O'Brien-Fleming spending function approach. According to the O'Brien-Fleming spending function approach, in the interim efficacy analysis based on OS, the one-side significance level is set as  $\alpha_1 = 0.0074$  in the interim analysis and  $\alpha_2 = 0.0228$  in the final analysis.

- In the interim analysis:  $P_1 \leq \alpha_1$ , early declaration of the trial will be considered according to actual results;
- In the final analysis:  $P_2 \leq \alpha_2$ , the between-group difference in OS will be considered statistically significant.

$P_1$  = the one-side P value in the interim analysis;  $P_2$  = the one-side P value in the final analysis;

The tests sequence and type I error in the final analysis are shown in the following figure:

[figure not shown]

A two-sided test with a significance level of  $\alpha=0.05$  will be used for secondary efficacy endpoints and safety analysis. Two-sided  $P \leq 0.05$  will be considered statistically significant with a 95%CI.

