#### **13.4.2 Analysis of Secondary Efficacy Endpoints**

##### **➤ ORR**

The number and percentage of subjects with an objective response (PR or CR) will be presented. The ORR and corresponding 95%CI will be summarized using F-distribution by binomial probabilities. The difference in ORR between intervention arms will be compared by the stratified Cochran-Mantel-Haenszel (CMH) test. Stratification factors as items specified in section 4.3.

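### Table S2 shows fewer iRECIST responders than Table S1 shows confirmed RECIST 1.1 responders in every arm, which does not fit the protocol's rule that iRECIST is applied only after RECIST 1.1 progression

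*Protocol*

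**What the plan says.** Three places in the protocol give the same order of assessment. The Synopsis (Criteria for evaluation, Efficacy) bases response mainly on RECIST 1.1 and then adds: "Namely, patients diagnosed with PD according to RECIST v1.1 were further identified by iRECIST to determine whether to take further observation". Section 5.4 says that "the efficacy evaluation will be assessed by RECIST v1.1 and further confirmed by iRECIST criteria". Section 9 explains that "patients identified as having disease progression as per RECIST v1.1 will be confirmed by iRECIST to determine further treatment". In each, the trigger for iRECIST is a RECIST 1.1 progression.

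Section 13.4.2 defines the response analysis briefly: "The number and percentage of subjects with an objective response (PR or CR) will be presented", with exact binomial intervals and a stratified Cochran-Mantel-Haenszel (CMH) test. It does not say which criteria apply. Section 3.6 names both RECIST 1.1 and iRECIST for investigator-assessed PFS and lists ORR and DCR after it in the same item.

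The supplementary results contain two tables, titled "Table S1. Tumor response as assessed by investigator review using RECIST 1.1" and "Table S2. Tumor response as assessed by investigator review using iRECIST". The response row of Table S1 is labelled "Objective confirmed response"; the matching row of Table S2 lacks the word confirmed. Both tables break patients down by best objective response and give CMH P values against EC alone.

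**The concern.** Up to the first RECIST 1.1 progression, iRECIST has not yet been invoked, so a patient's response record is the RECIST 1.1 record. After that point iRECIST can leave the progression unconfirmed, confirm it, or allow a later response. It can therefore add responders. It has no means of removing a CR, PR or SD recorded earlier. With the same patients and the same reader, the iRECIST table should show at least as many responders as the RECIST 1.1 table and no more patients with progression as their best response. Table S2 shows the opposite in all three arms.

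What is at stake is how far the iRECIST response rates, their intervals and their P values can be relied on. If Table S2 partly measures who later progressed, it is not a best-response table. The shortfall also differs between arms, so the differences between arms are affected as well as the rates.

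**Working it through.** **Inputs (Tables S1 and S2; arm 1 / arm 2 / control; N = 246 / 245 / 247)**

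| Best response | Table S1, RECIST 1.1 | Table S2, iRECIST | Net change |
|---|---|---|---|
| CR + PR | 188 / 187 / 145 | 157 / 139 / 112 | -31 / -48 / -33 |
| SD | 32 / 36 / 64 | 27 / 29 / 54 | -5 / -7 / -10 |
| Progression | 12 / 7 / 23 | 48 / 62 / 66 | +36 / +55 / +43 |
| NE | 14 / 15 / 15 | 14 / 15 / 15 | 0 / 0 / 0 |

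Progression in Table S2 is PD + iUPD + iCPD: 5+14+29 = 48, 3+13+46 = 62, 12+8+46 = 66.

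**Step 1: reproduce the printed figures.** Both tables sum to 246/245/247. Exact (Clopper-Pearson) intervals match all six printed ones, for example 70.6-81.6 for 188/246 and 57.5-69.8 for 157/246. For arm 2 against control by iRECIST, the unstratified CMH test gives P = 0.0116 against the printed stratified 0.0114; the strata are not shown, so a small gap is expected. The tables are internally sound. The problem lies between them.

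**Step 2: direction of the shift.** With N and NE equal in both tables, the losses in response and SD must equal the gain in progression (31+5 = 36, 48+7 = 55, 33+10 = 43). That balance carries no information about cause. The direction does: response and SD both fall, and only progression rises. The net shift is 36+55+43 = 134 of 738 patients. As a share of RECIST 1.1 responders, the net loss is 31/188 = 16.5%, 48/187 = 25.7% and 33/145 = 22.8%.

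**Step 3: the lower bound implied by the stated sequence.** If responses reached before progression stand, the iRECIST ORR is at least the RECIST 1.1 ORR:
- arm 1: at least 76.4%, printed 63.8%, shortfall 12.6 points
- arm 2: at least 76.3%, printed 56.7%, shortfall 19.6 points
- control: at least 58.7%, printed 45.3%, shortfall 13.4 points

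Disease control (CR + PR + SD) is 220/246, 223/245 and 209/247 = 89.4/91.0/84.6% from Table S1, against 184/246, 168/245 and 166/247 = 74.8/68.6/67.2% from Table S2.

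**Step 4: effect on the differences between arms.** Difference d = p1 - p2, with unstratified 95% CI d ± 1.96 × √[p1(1-p1)/n1 + p2(1-p2)/n2], in percentage points:

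| Contrast | Table S1 | Table S2 |
|---|---|---|
| Arm 1 - control | 17.7 (9.6 to 25.8) | 18.5 (9.8 to 27.1) |
| Arm 2 - control | 17.6 (9.5 to 25.7) | 11.4 (2.6 to 20.2) |
| Arm 1 - arm 2 | 0.1 (-7.4 to 7.6) | 7.1 (-1.5 to 15.7) |

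The unstratified P for arm 1 against arm 2 is 0.98 from Table S1 and 0.11 from Table S2.

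**Step 5: other explanations.** A stricter confirmation rule in Table S2 does not fit well: Table S1 is the table labelled confirmed, and failed confirmation would tend to move responders into SD, which also falls. A different reader or population is excluded by the titles and denominators. More missing assessments are excluded by the identical NE counts. Neither footnote explains the drop. A later iUPD or iCPD replacing an earlier CR, PR or SD fits all the margins.

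**The case against.** The strongest reply is that the Synopsis sentence and sections 5.4 and 9 govern what happens to a patient after progression. They do not define best overall response, and a derivation rule for iRECIST response may sit in a statistical analysis plan that is not shown. This stands in part. A reader might infer that the Synopsis sentence itself lets progression overwrite response; it says no such thing, and the absence of a best-response rule from the protocol is not in itself a fault. Section 3.6 also ties iRECIST most clearly to PFS, so an iRECIST ORR is not plainly a planned endpoint. But it is printed, labelled as best objective response, and tested. The printed figures still have to fit the stated sequence and Table S1, and they do not.

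Three stronger readings are tempting and are not supported:
- That 112 responders and 22 patients with SD were individually re-labelled as progression. These are net changes in margins; some responders may have moved to SD while some SD patients moved to progression. No patient-level data are shown.
- That the exact balance of losses and gains proves overwriting. It follows from equal N and NE under any mechanism.
- That the documents claim a response gain for TQB2450 over anlotinib alone. Both tables compare each arm with EC only. The 7.1-point gap is computed here, is not tested in the documents, and has an interval that includes zero.

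It is also fair that no headline conclusion changes: in Table S2 both experimental arms still exceed control (P<0.0001 and P=0.0114), and the fixed testing sequence contains only PFS and OS.

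**Conclusion.** Table S2 is inconsistent with Table S1 and with the order of assessment in the Synopsis and sections 5.4 and 9. The inconsistency is a net 36/55/43 patients placed in a progression class as best response, and an iRECIST ORR that is 12.6/19.6/13.4 points below the level the protocol's own sequence implies. Relative to RECIST 1.1, the advantage of arm 2 over control is understated (11.4 against 17.6 points), and a numerical, untested and non-significant gap between arms 1 and 2 appears (7.1 against 0.1 points).

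This rests on two assumptions: that Table S2 was built from the same investigator readings in the stated order, and that a response reached before progression counts as best response. The lower bound is not an estimate of the corrected rate, because responses after an unconfirmed progression could raise it. The mechanism is a probable inference from margins. The contradiction between the tables and the stated sequence does not depend on that inference. The primary endpoints are not affected.

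**What to change.** State, for iRECIST response analyses only, that a CR, PR or SD reached before iUPD or iCPD is kept as the best response, and that iUPD or iCPD counts as best response only when none of these came before it. Re-derive Table S2 on that rule: ORR, the category breakdown, confidence intervals and CMH P values. Add a programmed check that iRECIST responders are not fewer than RECIST 1.1 responders in any arm. Say in the footnote whether the iRECIST responses are confirmed.

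If Table S2 was meant to show something else, such as status after progression, relabel it, explain the derivation, and do not present it as best response or ORR.

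The cost is one sentence and the re-run of one table from data already held, with no new scans, readings or patients. The downside for the sponsor is that the arm 1 against arm 2 contrast by iRECIST is likely to become less favourable. Nothing about treatment after progression needs to change.
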